#### Study Design

A cross-sectional web-based survey will be administered in summer of 2022 to a nationally representative sample of Canadian women, aged 21 to 70 years, in English and French. The study population and inclusion criteria will be the same as those in study 1. Oversampling will be used to ensure that half of the sample is adequately screened and the other half is underscreened. Additional quotas will be used for the following factors: age, household income, and rural or urban residence (considering low cervical screening rates in rural Canada [7]) based on census data from Statistics Canada. Data collection will be conducted by Dynata, following the same procedure as that in study 2.

The questionnaire will follow the same structure and include the same sections as the survey detailed in study 1. Of the knowledge, attitudes, and beliefs items used for scale development in study 1, only those items retained after extensive psychometric analyses will be used in the study 2 questionnaire as part of the resulting shorter, validated scales. In addition, 2 previously validated measures, the extended HPV General Knowledge and HPV Vaccine Knowledge scales, will be added [69], given the relevance of HPV and HPV vaccination in cervical cancer. The measurement of the outcome variables (intentions to screen using the HPV test and self-sampling) is informed by PAPM [81], a categorical, stage-based model of health decision-making. As a binary, *yes or no* outcome limits accuracy, using a multistage model provides a more precise, nuanced understanding of women’s decision-making process that acknowledges the unique barriers associated with movement between each stage toward engaging with the behavior [90].

#### Sample Size

We calculated the sample size based on the estimation that approximately 30% of women will be in each of the PAPM adoption stages, *unengaged*, *undecided*, and *decided to*, and 10% will be in the *decided not* stage*.* As multinomial logistic regression can be considered as a series of binary logistic regressions, we based our calculations on the work of Peduzzi et al [91], which recommends a minimum of 10 observations per variable and the formula, N=10k/p, where N is the minimum number of observations needed, k is the number of predictor variables, and p is the smallest proportion in the binary model, that is, N = (10 × 15) / 0.25 = 600. Therefore, the minimum sample needed to reach sufficient power is 1500 because 40% of the sample (eg, unengaged+decided not) must represent 600 observations. Given that our objective is to estimate the association between psychosocial factors and intentions of HPV testing in both underscreened women and adequately screened women, we need 3000 (ie, 1500 in each group) valid responses to perform the analyses. Considering that an oversampling of maximum of 18% is required to account for careless responses, the approximate total number of survey responses needed is 3650.

#### Data Analysis

Corresponding to objective 1, we will conduct univariate analyses (means and proportions) for scale items (eg, knowledge and attitudes) and bivariate analyses (2-tailed *t* tests and chi-square tests) to estimate the differences between adequately screened women and underscreened women. We will calculate the effect size using Cohen *h* and Cohen *d* for proportions and continuous variables, respectively. Corresponding to objective 2, we will estimate the associations between psychosocial factors and intentions of HPV testing and self-sampling using multinomial logistic regression and model the log odds of PAPM stages (dependent variable) as a linear combination of the independent variables (eg, HPV testing knowledge and BWS preference scores). We will report odds ratios and 95% CIs of being in a PAPM stage versus the reference category (ie, unengaged) for each independent variable. Initially, we will conduct bivariate analyses to estimate the association between the outcome and independent variables. Then, independent variables showing significant associations (*P*<.10) will be entered simultaneously in the final model. We selected the following indices to report model fit: (1) Cox-Snell *R*^2^, (2) Cragg-Uhler *R*^2^, and (3) McFadden *R*^2^ [39,92]. We will use the Hausman-McFadden test to evaluate the final model for independence of irrelevant alternatives, which postulates that a person’s choice (ie, PAPM stage) is unchanged by other available choices (ie, fewer PAPM stages) [93]. Analyses will be conducted separately for underscreened women and adequately screened women. Analyses will be conducted using SPSS (IBM Corporation), R software (R Foundation for Statistical Computing), and STATA (StataCorp).

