### This Study

The proposed study will use a multistep approach to examine women’s knowledge, attitudes, beliefs, and preferences toward HPV testing and self-sampling. A preparatory study (study 1) was focused on the development and psychometric validation of scales measuring cervical cancer screening–related knowledge, attitudes, and beliefs. In addition, given the challenges of investigating women’s views toward a screening approach that has not yet been implemented, this study examined the feasibility and structure of a survey that examines these factors in Canadian women. Results of study 1 will yield validated scales to administer to a large sample of Canadian women (study 2) to estimate the associations between psychosocial factors and women’s intentions to participate in HPV-based screening programs. Furthermore, study 2 will survey and compare differences in psychosocial factors and HPV test intentions among adequately screened women and underscreened women, providing timely data to address emerging challenges in both groups.

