### Objectives

The main objectives of study 1 (scale and questionnaire development) are as follows:

To develop psychometrically valid scales to assess women’s knowledge of cervical cancer and attitudes, beliefs, and knowledge about HPV testing and self-sampling.To evaluate the feasibility and acceptability of using a web-based survey related to Canadian women’s knowledge, attitudes, beliefs, and preferences about new HPV testing–based cervical cancer screening programs.

The main objectives of study 2 (expanded population-based survey of Canadian women) are as follows:

To estimate differences in HPV and cervical cancer screening knowledge and attitudes, beliefs, and preferences regarding HPV testing between women who are adequately screened and those who are underscreened.To estimate the multivariable associations between psychosocial factors (eg, knowledge, attitudes, beliefs, and sociodemographics) and intentions to use HPV testing and self-sampling in women who are adequately screened and those who are underscreened.

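### Study 2 admits predictors to the multinomial model by a crude P<.10 screen, which can omit masked confounders and leave the two screening groups with differently adjusted odds ratios

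*Protocol article*

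**What the plan says.** The second main objective of study 2 is "To estimate the multivariable associations between psychosocial factors (eg, knowledge, attitudes, beliefs, and sociodemographics) and intentions to use HPV testing and self-sampling" in each screening group. The Data Analysis section for study 2 sets a two-step route to that estimate. "Initially, we will conduct bivariate analyses to estimate the association between the outcome and independent variables"; after that, "independent variables showing significant associations (*P*<.10) will be entered simultaneously in the final model". No variable is named as kept whatever its P value, and nothing elsewhere in the article softens the rule.

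The same section adds: "Analyses will be conducted separately for underscreened women and adequately screened women". There are two outcomes, as the study 2 Study Design section shows: "The measurement of the outcome variables (intentions to screen using the HPV test and self-sampling) is informed by PAPM". A separate model for each outcome is not stated word for word, but it follows, giving four models. On reporting, the section promises: "We will report odds ratios and 95% CIs of being in a PAPM stage versus the reference category (ie, unengaged) for each independent variable".

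The Sample Size section for study 2 takes 15 predictor variables and 10 observations per variable, and arrives at 1500 valid responses per group.

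**The concern.** The objective is estimation, but the gate is a crude significance test. A variable with a real adjusted association can show little crude association when it is correlated with another predictor that acts in the opposite direction. The screen then removes it, and the odds ratio of the other predictor is left unadjusted for it. Such patterns are plausible here. The article's Introduction describes perceived benefits and negative emotions as pulling acceptability in opposite directions, and psychosocial scales of this kind are likely to be correlated (my inference; the article gives no correlations).

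Three consequences follow:
- A construct that fails the crude test gets no adjusted estimate in that model, although one is promised for each independent variable.
- The CIs of the final model are computed as if its covariates had been chosen in advance.
- The screen is repeated in each group, so the two models may hold different covariates through chance alone. Readers who set the two tables side by side would be comparing odds ratios adjusted for different things.

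**Working it through.** **1. The plan's own sample size.** Stage shares are 30/30/30/10%, k = 15, and p = 0.10/(0.30 + 0.10) = 0.25.
- N = 10k/p = 10 × 15/0.25 = 600.
- 600/0.40 = 1500 per group, and 2 × 1500 = 3000.
- 3000/(1 − 0.18) = 3659, against the stated approximate 3650. The figure is reproduced.

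**2. Does entering 15 predictors without a screen fit that size?** The smallest stage holds 0.10 × 1500 = 150 women per group, and 150/15 = 10 per predictor. This meets the plan's own criterion. The screen itself does not hold the model to 15. The study 1 sections on sociodemographics and on health behaviours list 10 + 11 = 21 items before any scale or best-worst score is counted, and any number of them may pass P<.10.

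**3. Different covariate sets by chance.** Assume a 3-df test (four stages) in each group and identical true effects. Let r be the probability of passing P<.10, from a noncentral chi-square. A predictor enters exactly one of the two group models with probability 2r(1 − r).

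| Marginal power at .05 | r | In one group only |
|---|---|---|
| none (null) | 0.10 | 2 × 0.10 × 0.90 = 0.18 |
| 30% | 0.42 | 0.49 |
| 50% | 0.63 | 0.47 |
| 80% | 0.88 | 0.22 |

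Over four models, a null predictor has mixed status with probability 1 − 0.9⁴ − 0.1⁴ = 0.34. This last figure treats the four tests as independent. It is approximate, because both outcomes come from the same women. The two-group figures do not have that problem.

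**4. Possible bias: simulation A.** Four-stage multinomial logit, baseline shares 30/30/30/10%, n = 1500, 400 replicates per row. One predictor of interest (log OR b1) is always kept. One confounder (log OR b2) with correlation ρ is kept only if its crude test has P<.10. Results are for decided-to versus unengaged. All effects and correlations are assumptions.

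| ρ | b1 | b2 | ρb1 + b2 | Confounder dropped | True OR | Full model OR (coverage) | Screened OR (coverage) |
|---|---|---|---|---|---|---|---|
| 0.3 | 0.5 | −0.15 | 0 | 90% | 1.65 | 1.66 (95%) | 1.59 (92%) |
| 0.5 | 0.4 | −0.20 | 0 | 90% | 1.49 | 1.50 (96%) | 1.37 (72%) |
| 0.5 | 0.5 | −0.20 | 0.05 | 83% | 1.65 | 1.65 (95%) | 1.51 (71%) |
| 0.5 | 0.5 | −0.25 | 0 | 91% | 1.65 | 1.66 (95%) | 1.47 (61%) |
| 0.6 | 0.5 | −0.30 | 0 | 91% | 1.65 | 1.65 (93%) | 1.39 (28%) |

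The fourth column approximates the confounder's crude effect. It is zero in four rows and near zero in the other, so these rows show what happens under suppression, not what is typical.

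**5. Larger candidate lists, also with assumed effects.**
- *Simulation B:* 40 candidates, pairwise r = 0.3, suppressor pair r = 0.5, 150 data sets. For a true OR of 0.70 (decided-not versus unengaged), the screened model averaged 0.79 with 81% coverage. A prespecified 15-variable model averaged 0.71 with 95%. Here too the suppressor was set almost to cancel: log 1.19 = 0.174 against 0.5 × log 0.70 = −0.178.
- *Simulation C:* 20 candidates, same correlations, 200 runs, true OR 0.70, coverage taken when the key predictor was retained. With a same-direction second predictor (OR 0.84 or 0.70), screening gave 0.72 and 0.71 with 94% and 96% coverage. With no second effect it gave 0.74 and 89% (fixed set 0.70 and 91%). With a cancelling suppressor it gave 0.76 and 88%. With a stronger suppressor (OR 1.43), the key predictor was retained in only 47% of runs.

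**The case against.** Several points on the other side are sound.

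- *Bias is not certain.* A reader might infer that the reported odds ratios are biased and that their CIs cover less than 95%. The article gives no correlations or effects, so this cannot be shown. Simulations A and B were built around suppression; with effects in the same direction, simulation C shows almost no harm.
- *A fixed list protects only if it holds the right variables.* In the set-up of simulation C, a fixed 15-variable set lacking the second predictor gave 0.74, 0.62 and 0.79 (coverage 91%, 80% and 79%) for second-predictor ORs of 1.19, 0.70 and 1.43, against a true 0.70. The 95% coverage in simulation B assumes a well-chosen list.
- *The groups were not sized for a contrast of odds ratios.* A reader might infer this from "study 2 will survey and compare differences in psychosocial factors and HPV test intentions among adequately screened women and underscreened women". That sentence concerns levels of factors and intentions, which objective 1 compares by t and chi-square tests that the screen does not touch. The 1500 per group serves to fit a model in each. No test of odds ratios between groups is planned.
- *No covariate list exists yet.* The Health Belief Model and Theory of Planned Behavior guided questionnaire and item selection, and the scales await study 1. Candidates plausibly exceed 15, so some reduction is needed.

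None of this defends choosing covariates by crude P value. The rule is stated in the article, so it is not a detail left to a fuller document. The mismatch with objective 2, the CIs that ignore selection and the chance-driven covariate sets all remain.

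**Conclusion.** The concern holds in a conditional form. The P<.10 entry rule does not suit an objective of estimating multivariable associations: it can omit masked confounders and so can bias adjusted odds ratios, and its CIs take no account of the selection. The bias ranges from small or absent without confounding to material under suppression; the low coverage figures belong to assumed suppression of increasing strength and are not forecasts for this study. The risk of differing covariate sets needs no suppression. It affects odds ratios read side by side across groups, and by inference across outcomes. The planned size does not require the screen, since 15 prespecified predictors give 10 per variable in the smallest stage if the assumed stage shares hold. This should be changed; it does not invalidate the study.

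**What to change.** Delete the P<.10 entry rule. Once study 1 has fixed the scales, and before study 2 data are collected (collection had not begun as of May 2022), prespecify one covariate set on theoretical grounds: Health Belief Model and Theory of Planned Behavior constructs plus core sociodemographics, within the 15-predictor basis of the sample size. State how multi-category variables such as province count towards 15.

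Use the same set in both screening groups for a given outcome, and allow outcome-specific scales such as self-sampling attitudes. If candidates exceed 15, reduce them on theory or by penalisation, not by crude P values. Keep bivariate results as description only. A pooled model is needed only if the report claims that an association differs between groups; that claim should then rest on a group-by-predictor term.

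Cost: the team must agree the list in advance, some non-significant predictors stay in the tables, and CIs are slightly wider. On the plan's own criterion, no larger sample is needed.

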### Results

As of May 2022, data collection has not begun for study 2. Data collection is expected to begin in June 2022 or July 2022, and results are expected to be published in late 2022 and early 2023.

## Discussion

### Principal Findings

This study will use 2 complementary cross-sectional web-based surveys of Canadian women to develop psychometrically tested scales measuring cervical cancer knowledge, HPV testing knowledge, HPV testing attitudes and beliefs, and HPV self-sampling attitudes and beliefs and, then, include these scales in a broad survey to investigate the psychosocial correlates of women’s intentions to engage in HPV-based cervical cancer screening.

Scales developed in study 1 will be informed by measures in the extant literature and further enhanced by the generation of new items based on systematic evaluation of themes in the psychosocial literature on HPV testing. Using the TPB and HBM to guide item selection will further ensure that the scales provide meaningful insights into the factors affecting screening behaviors. Application of advanced psychometric methods, including item response theory, which facilitates the development of parsimonious measures [94], will help to ensure that the scales are comprehensive, while being brief and easy to administer. We expect the cervical cancer knowledge scale to expand on the psychometric methods applied for similar measures such as the Cervical Cancer Awareness Measure developed by Simon et al [44] and the HPV testing knowledge scale to show increased reliability compared with the existing subscale developed by Waller et al [48]. The HPV testing and self-sampling attitudes and beliefs scales will expand on existing measures by using advanced psychometrics in an up-to-date and representative sample. Accordingly, we expect our scales to represent a new measurement standard for investigating the attitudes, beliefs, and knowledge associated with HPV-based screening. In addition, the use of BWS to estimate preferences for cervical cancer screening will enable evaluation of women’s perceptions of trade-offs between different testing methods, and importantly, screening intervals and ages of initial screening. These changes have been barriers in other countries where HPV-based screening has been implemented [22,52].

Our expanded population-based survey (study 2) will provide comprehensive data to inform and support the development of Canadian HPV-based cervical cancer screening programs. Through objective 1, the specific evaluation of differences in knowledge, attitudes, and beliefs about HPV testing among women who are underscreened and those who are adequately screened will enable the development of targeted interventions to improve knowledge, address negative attitudes and beliefs, and reassure women about upcoming changes. In objective 2, analyzing the sociodemographic and psychosocial factors associated with screening intention stages will provide insight into developing interventions that consider the multiplicity of barriers to screening. Our investigation will offer a valuable response to calls to action to examine inequalities in cervical cancer screening in the interest of cervical cancer elimination [8]. Furthermore, by comparing women’s knowledge, attitudes, beliefs, and preferences toward HPV-based screening with the proposed guidelines, our findings will help to inform screening recommendations and ensure successful transition from cytology to HPV-based screening in Canada.

### Knowledge Dissemination Plan

To reach both research and health professional audiences, the study findings will be published in open-access, peer-reviewed scientific journals. Presentations will be made at national and international scientific meetings (eg, Canadian Association of Psychosocial Oncology, International Papillomavirus Society conference, and International Psycho-Oncology Society) and in webinars (eg, Consortium for Infectious Disease Control and International Papillomavirus Society). To reach policy makers, we will share a final research report with the Public Health Agency of Canada, CPAC, Canadian Task Force on Preventive Health Care, and provincial and territorial cancer screening program advisory boards. We will also share our results with nonprofit organizations such as the Canadian Cancer Society, the Society of Obstetricians and Gynaecologists of Canada, the College of Family Physicians of Canada, and HPV Global Action who have expressed strong interest in disseminating our results. We will produce content (eg, infographics) and engage with Canadian women on social media (Twitter, Facebook, etc). Research summaries will be drafted for dissemination to national media outlets to inform women about this public policy change and encourage discussions about HPV-based cervical cancer screening.

### Strengths and Limitations

A major strength of this study is the rigorous and comprehensive process to develop psychometrically validated scales informed by theoretical frameworks. In addition, examination of the feasibility of the developed questionnaire through study 1 will ensure that the survey used in study 2 will be easy to understand and relevant to Canadian women. BWS presents an innovative approach to assess preferences that controls for biases observed in typical multiple-choice or ranking assessments of preferences. The use of PAPM to examine intentions toward HPV testing and self-sampling will provide a theoretically informed and nuanced understanding of women’s decision-making compared with other studies using continuous or binary measures. Using a market research polling firm will enable time-efficient and cost-efficient recruitment and data collection. Furthermore, the web-based survey methodology will prevent the issue of missing data. Quota-based sampling will allow us to recruit a nationally representative sample based on recent census data. Attention check items and data cleaning techniques will allow us to identify and exclude unmotivated or *careless* responders, ensuring that high-quality data will be collected and analyzed.

The study design has some limitations. Relying on respondents’ self-report for their screening history of having had a Pap test in the past 3 years or not is subject to recall bias. Our anonymous web-based survey design prevents us from verifying it against health records data. To minimize this limitation, women will be provided with a reminder informative statement explaining what a Pap test is and how it is performed before asking them about their screening history. Given that the COVID-19 pandemic has prevented and continues to prevent women from engaging in cervical cancer screening, this may affect women’s report of their screening history and change the composition of women in our *underscreened* and *adequately screened* categories. It is not clear how this will affect our data, as the effect of the COVID-19 pandemic on screening access in Canada is not well understood in most provinces and territories [95]. To address this issue, we will include an item asking those participants who report being underscreened whether the COVID-19 pandemic had prevented them from receiving screening, and sensitivity analyses will be performed to examine the pandemic’s impact on screening. In addition, the lack of investigation at 2 different time points precludes any investigation of how intentions for HPV testing and self-sampling may relate to uptake and acceptability as these testing methods are introduced. Longitudinal examinations of acceptability and intentions toward HPV-based screening will be needed as implementation occurs in Canada. Unfortunately, our study design and recruitment strategy may preclude specific analyses in gender and sexual minority groups, considering the low case counts observed in population-wide web surveys (eg, 0.4% gender-diverse individuals in study 1). Recognizing the unique barriers faced by these groups in screening for cervical cancer, future research should specifically investigate the perceptions of gender and sexual minority Canadians toward HPV testing and self-sampling implementation [3,14,96]. Similarly, comprehensive understanding of cervical cancer screening and HPV in the First Nations, Inuit, and Métis populations is critical [5,34]. Our study could highlight certain issues in these populations (considering 2.9% representation in study 1), but unique participatory action initiatives involving relevant nongovernmental organizations and community advocacy groups are needed to fully understand their views and address their concerns.

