### Screening Landscape in Canada

In Canada, provinces and territories are in different planning phases for HPV-based cervical cancer screening programs [7,27], and the nationwide introduction of HPV-based primary screening is a key priority of the recent Canadian Partnership Against Cancer (CPAC) Action Plan for the Elimination of Cervical Cancer [5]. Although cytology-based screening is well established in Canada, screening coverage has failed to reach the CPAC target of including ≥80% of women [28]. This suggests that innovative approaches are needed to reach those women who are underscreened (ie, longer than 3 years since their previous Pap test or never screened). Approximately 40% of women in Canada diagnosed with cervical cancer report either never having had a Pap test or not having had one in >3 years [29]. Underscreened women are often members of ethnic, linguistic, gender, and sexual minorities or have lower socioeconomic status [30-33]. In Canada, only 65% of recent female immigrants reported having a Pap test in the previous 3 years, and 26% of non-English or French speakers reported never having a Pap test [29]. In a study of cancer screening registries in Ontario, transgender patients were significantly less likely than cisgender patients to be screened for cervical cancer (56% vs 72%) [32], reflective of barriers faced by transgender and other gender-diverse people in seeking cervical cancer screening [2]. A study by Decker et al [34] comparing screening rates and outcomes between First Nations women and all other women in Manitoba suggested lower screening rates among First Nations women aged ≥40 years and significantly higher rates of cervical lesions and cancers in First Nations women overall. Targeted solutions must consider these factors. For underscreened women, the introduction of HPV self-sampling could be important for ensuring that cervical cancer screening is more accessible and acceptable [13-15,35,36]. A meta-analysis of 37 studies by Nelson et al [37] found that women who used and indicated acceptability of self-sampling for future screening did so because of its convenience, privacy, and ease of use. However, identified barriers include women’s lack of confidence in their ability to correctly collect the specimen, lack of confidence in the test result, and discomfort with the procedure [37,38].

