##### Participants

The inclusion criteria were as follows: (1) born female; (2) aged between 21 years, which is the youngest age recommended to begin screening across provincial programs, and 70 years, which is the oldest age; (3) Canadian resident; and (4) intact cervix (eg, not having undergone hysterectomy). The exclusion criterion was having been diagnosed with cervical cancer previously. An oversampling quota was used to ensure that half of the sample was currently underscreened for cervical cancer (ie, >3 years since the previous Pap test or never screened) and the other half was adequately screened (ie, <3 years since the previous Pap test). Census-based quotas were used for primary language and province and territory of residence to reinforce sample representativeness.

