###### BWS Preferences

To analyze BWS preference data, we will use the counting and modeling approaches described by Aizaki and Fogarty [64]. Consistent with the counting approach, for domain A (screening interval) and domain B (age of initiation), we will calculate the best-minus-worst score (higher scores reflect higher preferences) for each attribute (eg, HPV test) and attribute level (eg, 3 years [for screening interval] and 25 years [for age of initiation]). For the modeling approach, we will use conditional logistic regression to model preferences as a function of the sum of the values of attributes and attribute levels [64]. For attributes and attribute levels, we will estimate odds ratios and 95% CIs.

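### Study 2 is called nationally representative although half of it is underscreened by quota; any overall estimate reported unweighted would lean toward underscreened women

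*Protocol article*

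**What the plan says.** The study 2 Study Design section describes a "nationally representative sample of Canadian women, aged 21 to 70 years, in English and French". The same paragraph states that "Oversampling will be used to ensure that half of the sample is adequately screened and the other half is underscreened" and adds census-based quotas for age, household income and rural or urban residence. Strengths and Limitations repeats the claim: "Quota-based sampling will allow us to recruit a nationally representative sample based on recent census data". The Conclusions again call the sample representative of Canadian women.

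Study 1 used the same split. Its Participants section says "An oversampling quota was used to ensure that half of the sample was currently underscreened for cervical cancer", and "Census-based quotas were used for primary language and province and territory of residence to reinforce sample representativeness".

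On the population, Screening Landscape in Canada says only that "screening coverage has failed to reach the CPAC target of including ≥80% of women".

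On analysis, the BWS Preferences section of study 1 says that "for domain A (screening interval) and domain B (age of initiation), we will calculate the best-minus-worst score" for each attribute and level, and that conditional logistic regression will give odds ratios with 95% CIs. It mentions neither screening group nor weights. The study 2 Data Analysis section, by contrast, compares the two screening groups and says that analyses are run separately in each.

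**The concern.** The claim and the design disagree. The article's own term for the 50:50 split is oversampling, which concedes that half exceeds the population share. The split is made on screening status, and the Objectives of study 2 rest on the expectation that the two groups may differ in knowledge, attitudes, beliefs and preferences. The limitations discuss recall, COVID-19, the single time point and small minority subgroups, but not this.

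What is at stake is how overall figures will be read. The Discussion says that findings will be compared with proposed guidelines and will inform screening recommendations, and the dissemination plan includes national agencies and the media. A reader told that the sample is nationally representative will take an overall preference or knowledge figure as the view of Canadian women. If it is unweighted and the groups differ, it is not, and a larger sample does not reduce the error.

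**Working it through.** **1. The plan's own figures, and the 1:1 split.**
- Study 2: smallest proportion p = 0.10 / 0.40 = 0.25; N = 10 × 15 / 0.25 = 600; 600 / 0.40 = 1500 per group; two groups give 3000 valid responses; 3000 / 0.82 = 3659, against about 3650 stated.
- Study 1: 2 × 500 / 0.82 = 1219.5, or 1220 as stated; 1027 valid responses were retained.

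The figures reproduce to rounding, and the study 2 calculation confirms equal groups.

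**2. The population share u.** Coverage below 80% gives u above 20%, taking underscreened as the complement of coverage. The article gives no exact share. For an upper end I use 35%, the complement of the statement that "only 65% of recent female immigrants reported having a Pap test in the previous 3 years". That figure describes a subgroup, so the range 20% to 35% is an assumption, not an estimate.

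**3. Formulas, for a sample split 50:50.**
- Over-representation of underscreened women = 0.5 / u
- Shift of an unweighted overall mean or proportion = (0.5 − u) × (underscreened value − adequately screened value)
- Correcting weights = u / 0.5 and (1 − u) / 0.5
- Design effect of those weights (Kish) = 2 × [u² + (1 − u)²]

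| u (assumed) | Over-representation | Shift, as fraction of group difference | Weights (under / adequate) | Design effect | Effective n of 1027 | Effective n of 3000 |
|---|---|---|---|---|---|---|
| 0.20 | 2.50 | 0.30 | 0.40 / 1.60 | 1.36 | 755 | 2206 |
| 0.28 | 1.79 | 0.22 | 0.56 / 1.44 | 1.19 | 860 | 2513 |
| 0.35 | 1.43 | 0.15 | 0.70 / 1.30 | 1.09 | 942 | 2752 |

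**4. What this means in points.** The group difference is not known, so these are illustrations.
- Difference of 10 points: shift of 0.15 × 10 = 1.5 to 0.30 × 10 = 3.0 points.
- Difference of 20 points (60% against 40%): the unweighted figure is 50.0%; the weighted figure is 0.20 × 60 + 0.80 × 40 = 44.0%, or 0.35 × 60 + 0.65 × 40 = 47.0%. The shift is 3.0 to 6.0 points.
- Yardstick: the 95% half-width for a proportion near 50% is 1.96 × √(0.25 / 1027) = 3.1 points in study 1, and 1.96 × √(0.25 / 3000) = 1.8 points for an overall figure at the study 2 size.

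**5. Which results the formula covers.** It is exact for proportions and for mean scores, including a mean best-minus-worst score. For odds ratios from a conditional logit it gives the direction, not the exact size. Within one screening group the shift is zero, as it is if the groups do not differ. The split after data cleaning in study 1 is not reported; I take it as still about 50:50.

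**The case against.** The strongest reply is that the planned analyses largely avoid the problem. The Introduction says that examining the two groups' preferences separately is useful, study 2's first objective is the difference between the groups (preferences included), and its analyses are run separately with 1500 women sized for each. Study 1 exists for scale validation and feasibility, and its design section calls the sample national, not representative. The promise to compare preferences with guidelines belongs to study 2. The oversampling is stated openly, and the strength claim refers to census data, so it can be read as a match on the quota variables. All of this stands, and it limits the consequence. It does not cure the wording: representativeness is claimed without that qualification in three places, and an unseen fuller plan cannot make a half-underscreened sample representative on screening status.

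Two stronger readings are tempting.

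- A reader might infer that the article plans a pooled, unweighted BWS analysis. It does not say so. The BWS section is silent on pooling, stratifying and weighting, and an article may leave such detail to the full plan. What can be said is that the section, followed as written, gives one set of scores and odds ratios per domain.
- A reader might also infer that the census quotas fit neither screening group, since underscreened women are said often to have lower socioeconomic status. The article does not say whether those quotas apply overall or within each half, so this cannot be concluded.

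**Conclusion.** The point holds as a contradiction between description and design, with a conditional consequence. Study 2 can at most match the census on its named quota variables; it is not representative of Canadian women on screening status. The group-specific estimates planned for study 2 are not shifted by the quota. Any overall estimate reported unweighted is shifted toward underscreened women by 0.15 to 0.30 of the group difference, and the study 1 BWS scores and odds ratios are the most plausible case.

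This size rests on an assumed u of 20% to 35% and on the groups differing. With a 10-point difference, the shift in study 1 stays within the 3.1-point half-width; with a 20-point difference, it is about equal to it or up to roughly twice it.

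**What to change.** 1. In the study 2 Study Design, Strengths and Limitations, and Conclusions, describe a quota sample with two equal screening strata, matched to the census only on the named quota variables.
2. State that BWS and descriptive results are reported by screening group in both studies.
3. Weight any overall figure to a cited population share of underscreened women, and show the result over a range of shares if the source is uncertain.

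The article reports that study 2 data collection had not begun as of May 2022, so none of this touches recruitment. The work is wording, one sourced figure and a weight variable. The statistical cost falls on overall figures only: for the two-stratum weight alone, a design effect of about 1.09 to 1.36, which makes confidence intervals √1.09 = 1.04 to √1.36 = 1.17 times as wide (4% to 17% wider). Raking to further variables would add to that. Reporting by group needs no weight for the screening quota, but each group's estimates rest on about half the sample.
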